## 4. Work Proposed

### 4.a. Overview

90 eligible male veterans with chronic PTSD will be randomly assigned to treatment with 600 mg/day mifepristone or placebo for one week and assessed for clinical outcomes at one and three months follow-up. Eligibility will be based on the inclusion and exclusion criteria which are enumerated below and in the Human Participants section. The inclusion and exclusion criteria were selected in order to include as representative a sample as possible while also addressing safety concerns. Veterans who are actively suicidal as assessed by the Columbia-Suicide Severity Rating Scale (C-SSRS) or who have attempted suicide within the past two years will be excluded. (If suicidality is identified, the necessary steps will be taken to ensure the appropriate clinical care is provided, and the local suicide prevention policies implemented.) Veterans with adrenal insufficiency will be excluded, as will veterans with other major medical or neurological illnesses, as they may be at increased risk of developing adverse events. Veterans with renal disease/impairment, hepatic disease/impairment, cardiac illness (e.g. coronary vascular disease, congestive heart failure), or hypokalemia at screening will also be excluded. Since mifepristone use can prolong the QTc interval in a dose-related manner, veterans with a prolonged QTc interval, defined as >450 msec, on the ECG at screening will be excluded. To evaluate QTc prolongation post-mifepristone treatment, an ECG will also be performed at both the 3 day follow up visit (visit 1.5) and 1 week follow-up visit (week 1, visit 2).

Participants on potent CYP3A4 inhibitors (fluconazole, ketoconazole, itraconazole, erythromycin, rifampin) and some anticonvulsants (e.g., phenytoin, phenobarbital, and carbamazepine) will be excluded since these medications impact the metabolism of mifepristone (see Risk/Benefit Assessment for details). Due to an increased risk of adverse drug reactions, veterans taking simvastatin, lovastatin, fentanyl, pimozone, bupropion, nefazodone, dihydroergotamine, ergotamine, quinidine, sirolimus, carvedilol, propranolol, diltiazem, verapamil, alprazolam, or tacrolimus will also be excluded. Since the impact of mifepristone on the male reproductive system has not been extensively studied, only veterans willing to use effective means of birth control for up to 90 days after mifepristone ingestion will be eligible; this will cover the critical period of fetal development.

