#### 4.a.2. Exclusion Criteria

1. Veteran recently continued to engage in a maladaptive pattern of alcohol/substance use and/or abuse (as defined in protocol).
2. Veteran has used potent CYP3A4 inhibitors (fluconazole, ketoconazole, itraconazole, erythromycin, rifampin) and inducers within five half-lives prior to randomization.
3. Veteran is taking simvastatin, lovastatin, fentanyl, pimozide, bupropion, nefazodone, dihydroergotamine, ergotamine, quinidine, sirolimus, tacrolimus, or clarithromycin, cyclosporine, St. John's Wort, diltiazem, verapamil, propranolol, alprazolam, carvedilol or some anticonvulsants (phenytoin, phenobarbital, or carbamazepine) within five half-lives prior to randomization.
4. Veteran is taking oral corticosteroids within five half-lives prior to randomization.
5. Veteran should be free of a major medical illness and medical condition that contraindicate the administration of mifepristone. These include but are not limited to:
  - a. Veteran has a history of adrenal insufficiency or a low plasma cortisol level at screening (a.m. level less than 5 mcg/dl or a p.m. level of less than 3 mcg/dl.)
  - b. Veteran has a history of severe traumatic brain injury, a history of a stroke, or another neurological illness or injury likely to impact cognitive functioning.
  - c. Veteran has diabetes mellitus, an endocrinopathy, or another major medical illness.

- d. Veteran has a history of cardiovascular disease including a history of angina, myocardial infarction or other evidence of coronary artery disease, or congestive heart failure
  - e. Veteran has prolonged QTc interval >450 msec on ECG at screening.
  - f. Veteran has hypokalemia at screening (defined as potassium level < 3.5 mEq/L)
  - g. Veteran has a history of hepato-biliary disease or an AST, ALT greater than 2X the ULN.
  - h. Veteran has a history of renal disease or an estimated GFR of < 60 ml/min.
6. Veteran has a lifetime diagnosis of schizophrenia, schizoaffective disorder, or type I bipolar disorder.
  7. Veteran has a history of attempted suicide within the previous two years or active suicidal ideation within the past month as assessed by the Columbia-Suicide Severity Rating Scale (C-SSRS).
  8. Veteran is currently receiving specialized trauma-focused psychotherapy, such as prolonged exposure therapy and cognitive processing therapy.
  9. Veteran is not willing to use effective means of birth control during the study.

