  10. Veteran has a history of allergic reaction to mifepristone.
  11. Veteran is found to be unsuitable for study participation at the discretion of the site investigator for any reason.

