#### 4.d. Randomization

Prior to randomizing a patient, all screening and baseline evaluations must be completed and the patient determined to be eligible for inclusion in the study. Randomization should occur no later than two weeks from the completion of the screening visit.

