#### 4.e. Treatment Algorithm

Medication treatment will be for one week duration, and randomized participants will be given a seven-day supply of medication. Three weeks after the pulse treatment, the participant will undergo clinical reassessment. If participants develop an AE or as SAE that is deemed unsafe by the PI, they will be taken off treatment immediately but will be followed per protocol. The research team does not anticipate the occurrence of study-related SAEs, as the dose levels used in this trial have been used before in other studies without SAEs. In our pilot study of mifepristone in PTSD, no veterans were taken off treatment.

Both the active study medication and its matching placebo will be donated by Corcept Therapeutics.

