Common Terminology Criteria for Adverse Events (CTCAE) and Common Toxicity Criteria (CTC). Common events known to be associated with mifepristone will be assessed using the reference toxicity table included in the study manual of operations to decrease the variability across investigative sites. Per the FDA's request, the investigators will explicitly inquire about the development of a rash since this is a known side effect of mifepristone. Medication will be discontinued if a rash develops or adrenal insufficiency is suspected; for the latter, a referral to internal medicine and/or endocrinology will be made. If the rash is severe or persistent, the veteran should be referred to a dermatologist.

With respect to suicidality, veterans with a history of attempted suicide within the previous two years or active suicidal ideation within the past month (participant endorses active suicidal ideation with any methods without intention to act (question 3)), as assessed by the C-SSRS, will be excluded. For all study participants, suicidality will be re-assessed at in-person post-treatment visits (one week follow-up, one month follow-up, and three month follow-up) using the C-SSRS. If the participant develops active suicidal ideation (as elicited from the C-SSRS or spontaneously reported) at any point in the study, he will be further assessed; the appropriate clinical intervention will be initiated and the local procedures for notifying the suicide prevention coordinator will be followed.

To assist in monitoring patient safety, the sites will be provided with an Investigational Brochure (IB) prepared by Corcept Therapeutics and a Drug Information Report (DIR) that is prepared and updated as needed by the pharmacy coordinating center study clinical pharmacist. The DIR provides a comprehensive review of the published literature regarding mifepristone safety data as used in the treatment of psychiatric disorders. The IB and DIR are submitted along with the protocol to the IRB, the DMC, and to the FDA as part of the IND as the safety information for the study. The statistical coordinating center then distributes the IB, DIR, protocol, and Drug Treatment and Handling Procedure manual to the study sites.

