##### Primary Outcome:

Primary Analysis of Primary Outcome -The primary analysis for this study will not be based on a hypothesis test; rather, responder rates at one month will be calculated for each of two groups. If mifepristone 600 mg is observed to have at least a 15% higher responder rate than placebo, then we are at least 90% certain we have detected a clinically relevant signal. This analysis will be performed based on a modified intent-to-treat (mITT) principle. All randomized participants will be included in the analyses except for those for whom there is positive proof that they did not take a single dose of study medication (e.g. medication never picked up, full bottle returned, patient immediately declines participation after study medication has been dispensed) or there is positive proof that they are deemed ineligible after randomization and are terminated in the 7-day treatment phase due to safety concern. For patients who do not have one-month CAPS total score, their responses will be estimated using multiple imputation technique as outlined in Molenberghs and Kenward, 2007, Chapter 9 and implemented in the SAS procedure MI using participants aforementioned baseline characteristics and available information at other time points (baseline, 1 week, 12 week). The imputation will be done within each treatment group.

Secondary Analysis of Primary Outcome -The primary outcome will also be compared using chi-square tests. Additionally, logistic regression models will be used to adjust for aforementioned baseline characteristics. The model selection will use a backward elimination procedure and be verified by a forward selection procedure.

Exploratory Analysis of Primary Outcome -The primary outcome will also be explored for subgroups as defined by concurrent psychotropic medication use status and classification prior to randomization. The mITT principle will also be applied in the secondary and exploratory analyses of the primary outcome.

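### The second mITT exclusion makes an on-treatment safety termination a condition for leaving the primary analysis set, and so can bias the responder comparison

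*Protocol*

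**What the plan says.** Section 4.p.1 (Primary Analysis of Primary Outcome) builds the mITT set from all randomized participants, less two groups. The first is those for whom there is "positive proof that they did not take a single dose of study medication". The second is those who are, again with proof, "deemed ineligible after randomization and are terminated in the 7-day treatment phase due to safety concern". The two conditions in the second exclusion are joined, so both must hold. Nothing confines it to undosed participants.

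The primary analysis compares observed responder rates at one month. A signal is declared if mifepristone is at least 15 percentage points above placebo, and no hypothesis test is made. The same mITT set serves the secondary, exploratory and descriptive efficacy analyses. The three procedures under Sensitivity Analysis of Missing Data replace or omit missing week-4 scores within those analyses. Only the safety population keeps every dosed participant.

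Other sections bear on how the exclusion would be read:

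- Section 4.d requires that before randomization "all screening and baseline evaluations must be completed and the patient determined to be eligible for inclusion in the study".
- Section 4.a.2 ties the ECG criterion to entry ("Veteran has prolonged QTc interval >450 msec on ECG at screening") and does the same for potassium. Its last criterion is open: "Veteran is found to be unsuitable for study participation at the discretion of the site investigator for any reason".
- Section 4.a states "Since mifepristone use can prolong the QTc interval in a dose-related manner", and section 4.i states "Medication will be discontinued if a rash develops or adrenal insufficiency is suspected".
- Section 4.e says of participants with an adverse event judged unsafe that "they will be taken off treatment immediately but will be followed per protocol".

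**The concern.** Leaving out people who never took a dose does little harm in a blinded trial, because the treatment cannot have caused the exclusion. The second exclusion is different. Take two participants with the same eligibility defect, both dosed. If one is terminated for safety in the first week and the other is not, the first leaves the primary set and the second stays. Membership then depends on something that happened after randomization and that mifepristone can influence. Blinding does not remove this, because the drug can produce the triggering event without anyone knowing the arm.

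The ineligibility condition narrows the group but does not settle the matter. The text lets ineligibility be declared after randomization and does not say that it must rest on facts that existed beforehand. The open-ended investigator-discretion criterion leaves room for a judgement formed during treatment.

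The result is a raw rate difference set against a fixed cut-off with about 45 per arm, so one or two people can move it across the line. That comparison informs the decision on a Phase III trial. No planned analysis puts the excluded participants back.

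**Working it through.** **Inputs from the protocol.** Section 4.n.2: 90 randomized, 45 per arm; 20% attrition, hence 72 completers (36 per arm); placebo response 40%; difference of interest 15 points; 90% probability of correct selection. Section 4.p.1: the decision rule is an observed difference of at least 15 points. Section 2.a.3: rash in 3.3% at 600 mg/day.

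**Input not in the protocol.** The number k excluded under the second rule. I take k = 0 to 5, all from mifepristone, as an illustration.

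**The plan's own figure first.** With 36 per arm and rates of 40% and 55%, SE = √[(0.40×0.60 + 0.55×0.45)/36] = √(0.4875/36) = 0.1164. Then Φ(0.15/0.1164) = Φ(1.289) = 0.901. The exact binomial calculation, with ties split equally, gives 0.899. Attrition: 72/0.80 = 90. The sample size reproduces and is not in question.

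**Effect on the rate.** If the true rate is 40% in all 45 mifepristone participants and the k removed are all non-responders, the rate among those kept is 0.40×45/(45 − k) = 18/(45 − k).

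**Effect on the decision.** The exact binomial probability of an observed difference of at least 15 points, with placebo at 45 participants and 40%, and mifepristone at 45 − k participants:

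| k removed | Kept rate if all removed are non-responders | Inflation (points) | P(≥15 points), all removed are non-responders | P(≥15 points), removed respond at 40% |
|---|---|---|---|---|
| 0 | 40.0% | 0 | 8.1% | 8.1% |
| 1 | 40.9% | 0.9 | 8.0% | 6.7% |
| 2 | 41.9% | 1.9 | 11.5% | 8.4% |
| 3 | 42.9% | 2.9 | 11.7% | 7.2% |
| 4 | 43.9% | 3.9 | 15.8% | 8.4% |
| 5 | 45.0% | 5.0 | 17.6% | 7.9% |

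The uneven steps come from the small whole-number denominators. If the same k non-responders are kept in the denominator, the probability is 8.0, 7.9, 7.8, 7.7 and 7.6% for k = 1 to 5.

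**One concrete trial result.** 24/45 against 18/45 is 53.3% − 40.0% = 13.3 points, no signal. Remove one mifepristone non-responder: 24/44 − 18/45 = 14.5 points, still no signal. Remove two: 24/43 − 18/45 = 55.8% − 40.0% = 15.8 points, a signal.

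**How large k might be.** The rash figure implies 0.033×45 ≈ 1.5 mifepristone participants with a rash. A rash alone is not ineligibility, so this does not estimate k. It shows only that safety stops on mifepristone may be few, and k could be zero.

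**The case against.** The strongest defence is that the rule is narrow. It demands proof and both conditions together. Section 4.d settles eligibility before randomization, so the natural reading is a participant later found to have been ineligible at entry, for whom continued dosing was unsafe. Few such cases are likely: section 2.a.3 reports no significant differences in the listed side effects in the largest earlier trial, and section 3 reports no adverse events in the pilot. The inflated probabilities need every excluded participant to be a non-responder on mifepristone, whereas the plan assumes 40% response even on placebo. Section 4.p.1 also calls the results hypothesis generating. All of this stands as a limit on the likely size. It does not repair the rule: the natural reading is not what the text says, and even under that reading the safety termination still decides which ineligible participants leave.

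Three stronger readings are tempting but lack support:

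- A reader might infer that every dosed participant stopped for safety is dropped. The joint condition rules this out.
- A reader might infer a conflict with section 4.e, so that week-4 CAPS is collected after an adverse-event stop and then thrown away. Section 4.e covers people who are not thereby ineligible; they stay in mITT, and the two passages are compatible.
- A reader might infer that a long QTc or low potassium at day 3 makes a participant ineligible. Section 4.a.2 ties both criteria to screening, so an on-treatment value does not itself breach them. Any route from an on-treatment finding to ineligibility runs through the general wording, chiefly the discretion criterion.

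**Conclusion.** The point holds as a defect in the definition of the primary analysis set. The second exclusion can remove dosed participants, is conditional on an event that treatment can affect, does not anchor ineligibility to pre-randomization facts, and is not undone by any stated sensitivity analysis. It can bias the result; the protocol does not show that it will.

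The size is not determinable from the protocol. With 0 to 5 exclusions from mifepristone alone, the inflation lies between 0 and 5 points against a 15-point threshold. The upper end, and the probability of about 18%, rest on all five being non-responders. If those excluded respond like the rest, there is no upward shift. If exclusions fall equally on both arms with similar response, the expected bias is about zero. Should-fix, with moderate confidence in the size of the effect.

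**What to change.** Delete the second exclusion from the mITT definition in section 4.p.1. If the sponsor wishes to keep an ineligibility exclusion, limit it to a named entry criterion shown by data collected before randomization to have been violated. That judgement should be made blind to arm and outcome, and without regard to anything that happened on treatment.

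All other participants who took at least one dose stay in mITT. They contribute their observed week-4 CAPS, or are handled by the missing-data rules already stated if it is absent.

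If any such exclusion is kept, add a sensitivity analysis of the primary outcome in all dosed participants.

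The cost is about a sentence in the analysis-set definition and, where needed, one extra analysis. The sample size stays at 90 and no rule on stopping treatment is touched. The observed mifepristone responder rate may be slightly lower. If no one would have been excluded, nothing changes.

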#### 4.d.1. *Randomization Methods*

The randomization scheme and associated codes will be developed by the Hines Cooperative Studies Program Coordinating Center (CSPCC). Permuted block randomization will be employed to assign patients to 600 mg mifepristone or placebo. Randomization will be stratified by study site.

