#### 4.p. Statistical Analyses

##### 4.p.1. Analysis Plan

The randomization will be assessed by comparing the distribution of all baseline characteristics including age, race, marital status, education, duration of symptoms, duration of illness since trauma, overall extent of the psychiatric co-morbidity, whether or not on concurrent psychotropic medications and number of those medications used prior to randomization, baseline total CAPS score, military cohort, and site across the two randomized groups.

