#### Secondary Outcomes:

1. The analysis specified for the one-month responder rate will also be done for the three-month responder rate as a secondary analysis to check for the sustainability of the response.

Additionally, a continuous mixed-effects model for longitudinal observations of CAPS (past week symptom status) scores (week 1, 4 and 12) will be used. Covariates including baseline characteristics, specifically duration of symptoms, duration of illness since trauma, concurrent psychotropic medication use prior to randomization, overall extent of the psychiatric co-morbidity, military cohort, and site will be explored in the adjusted analysis. This analysis will provide a treatment effect in terms of the slope of the interaction term between group and time variables, conditional on aforementioned covariates under the missing at random (MAR) assumption (Laird and Ware, 1982).

The above mentioned analyses will be performed based on a mITT principle.

2. To describe the safety and tolerability mifepristone, information on all related and unrelated SAEs will be collected. There will be accelerated safety reporting for every two adverse events in every ten participants. The specific AE(s) leading to the withdrawal of a patient from study participation will be collected, along with characteristics of the AE including severity, duration, and whether the withdrawal was at the request of the patient or was initiated by a study investigator or other clinician. The AE rate will be determined on the basis of occurrence of at least one adverse event in each participant, and the following comparisons will be carried out:
  - a. A comparison of individual adverse event rates between mifepristone and placebo.
  - b. A comparison of overall adverse event rates between mifepristone and placebo.
  - c. A comparison of severity of adverse events (grades 1, 2, 3, 4, and 5) between mifepristone and placebo
  - d. A comparison of overall adverse event rates classified as possibly or definitely attributable to study drug, between mifepristone and placebo.
  - e. A comparison of overall adverse event rates classified as possibly or definitely attributable to study drug, between mifepristone and placebo by weeks 1, 4 and 12.

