#### Descriptive Outcomes:

Descriptive statistics and confidence intervals for the change from baseline to one month follow-up and to three month follow-up for each of the two treatment groups will be provided for each of the descriptive outcome measures. Additionally, comparisons between mifepristone and placebo will be performed; however, lack of statistical significance should not be construed as evidence of no clinical effect given the small sample size. All efficacy analyses on descriptive outcomes will be performed based on a mITT principle.

1. PTSD Symptom Sub-Scales
  - a. Descriptive statistics for the change in score from baseline to one month on the three PTSD symptom sub-scales (intrusions, hyperarousal, and avoidance) and confidence intervals will be provided for each treatment group.
  - b. Change in score from baseline to one month on the three PTSD symptom sub-scales (intrusions, hyperarousal, and avoidance) will be compared between mifepristone and placebo using two-sample t-test (or Wilcoxon rank-sum test if the normality assumption does not hold).
2. Depression
  - a. Descriptive statistics for the change in score from baseline to one month on the Beck Depression Inventory (BDI) and confidence intervals will be provided for each treatment group.
  - b. Change in score from baseline to one month on the Beck Depression Inventory (BDI) will be compared between mifepristone and placebo using two-sample t-test (or Wilcoxon rank-sum test if the normality assumption does not hold).
3. PTSD Symptom Severity

- a. Descriptive statistics for the change in score from baseline to one month on the PTSD Checklist (PCL) and confidence intervals will be provided for each treatment group.
- b. Change in score from baseline to one month on the PTSD Checklist (PCL) will be compared between mifepristone and placebo using two-sample t-test (or Wilcoxon rank-sum test if the normality assumption does not hold).
4. Sleep Quality
- a. Descriptive statistics for the change in score from baseline to one month on the Pittsburgh Sleep Quality Index (PSQI) and confidence intervals will be provided for each treatment group.
- b. Change in score from baseline to one month on the Pittsburgh Sleep Quality Index (PSQI) will be compared between mifepristone and placebo using two-sample t-test (or Wilcoxon rank-sum test if the normality assumption does not hold).
5. Anger

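### The adjusted responder model selects from 12 baseline characteristics with too few responders, so its treatment test runs at roughly 6-8%; the change-score tests also forgo baseline adjustment

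*Protocol*

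**What the plan says.** Section 4.d.1 of the protocol states: "Randomization will be stratified by study site". Section 4.p.1 lists 12 baseline characteristics: age, race, marital status, education, duration of symptoms, duration of illness, extent of psychiatric comorbidity, psychotropic medication use, number of such medications, and finally "baseline total CAPS score, military cohort, and site across the two randomized groups".

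Under Primary Outcome, the secondary analysis has two parts:
- An unadjusted test: "The primary outcome will also be compared using chi-square tests".
- An adjusted version, in which "logistic regression models will be used to adjust for aforementioned baseline characteristics", with this rule for choosing among them: "The model selection will use a backward elimination procedure and be verified by a forward selection procedure".

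Missing week 4 responses are multiply imputed within treatment group. The analyses are repeated under three other missing-data procedures, and Secondary Outcomes item 1 repeats the responder analysis at three months.

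Under Descriptive Outcomes, items 1b to 7b compare change from baseline between arms without a baseline or site covariate. For depression: "Change in score from baseline to one month on the Beck Depression Inventory (BDI) will be compared between mifepristone and placebo using two-sample t-test", with a Wilcoxon test as fallback if normality fails. The same wording covers the CAPS subscales, PCL, PSQI, STAXI, CAPS item 24, cortisol and ACTH.

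Apart from the primary analysis, tests are two-sided at 5%.

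**The concern.** A logistic model offered many candidate terms with few responders gives an unreliable treatment test. The standard error printed for the selected model does not reflect the search that produced it. Selection may discard the factor on which randomisation was stratified, or the baseline value of the outcome scale.

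There is also a problem of reproducibility. Each imputed data set, each missing-data procedure and each time point can yield its own covariate set. A shift in the treatment effect between sensitivity analyses may then reflect different covariates and not the missing data those analyses are meant to examine.

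For the continuous descriptive outcomes, a t-test on change leaves unused a baseline measurement that is already collected. This is a question of precision, not of validity.

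**Working it through.** **Size of the trial.** Section 4.n.2 gives 90 randomised, 72 completers (72/0.8 = 90), a 40% placebo response and a 15-point difference. At 36 per arm and 40% versus 55%, the exact probability of correct selection, ties split equally, is 0.899, so the plan's 90% reproduces.

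**Responders per candidate term.**
- Lowest: 0.40 × 72 = 28.8, about 29 responders (no effect, completers only).
- Highest: (0.40 + 0.55)/2 × 90 = 42.75, about 43 responders (full effect, all randomised).
- The 12 characteristics give about 16 to 20 model terms, depending on coding.
- Responders per term: 28.8/20 = 1.4 to 42.75/16 = 2.7.

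**Error rate of the treatment term.** Trials were simulated with no treatment effect, about 40% responders, randomisation in blocks within site, 12 candidate characteristics, treatment forced in and two-sided 5% Wald tests. Assumptions not in the protocol are the stay level, covariate strength, block size of 4, and pooling of small sites. Each row is 3,000 trials (Monte Carlo SE about 0.4-0.5 points), except the last, which is 1,500.

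| Scenario | Backward elimination | All 12, no selection | Treatment + site + baseline CAPS | Chi-square |
|---|---|---|---|---|
| n=90, stay 0.05 | 7.2% | 7.8% | 5.8% | 5.3% |
| n=90, stay 0.10 | 7.5% | 7.8% | 5.8% | 5.3% |
| n=72, stay 0.10 | 8.1% | 7.9% | 5.8% | 4.7% |
| n=90, stay 0.10, no prognostic covariate | 7.0% | 7.3% | 5.6% | 5.3% |
| n=90, stay 0.10, strong covariates | 7.5% | 7.3% | 5.8% | 4.9% |
| n=90, stay 0.10, forward also run | 7.6% | 7.9% | 5.4% | 5.0% |

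In the last scenario forward selection gave 7.3%. Counting a positive result from either procedure gave 7.9%.

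Three further simulations with other settings agree:
- n=80, 5,000 trials, only baseline CAPS prognostic, stay 0.05: 6.9% after backward elimination, 4.8% for the short fixed model.
- n=80, 2,000 trials: 5.7% (stay 0.05) and 7.2% (stay 0.10), against 4.9% and 5.5% for the short model. Backward and forward chose different models in 8-15% of trials, and baseline CAPS was dropped in 20-31%.
- A separate repeat: 6.4-7.9% backward, 7.2-8.9% full model, 5.3-6.0% short model, 4.5-5.6% chi-square.

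The second and third columns of the table are practically the same. The excess therefore comes mainly from the number of terms offered, not from selection alone.

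**Change scores versus ANCOVA.** Let k be the follow-up/baseline SD ratio and r the baseline/follow-up correlation. Then

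Var(ANCOVA)/Var(change) = k²(1 − r²)/(1 + k² − 2rk).

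With k = 1 this is (1 + r)/2: 0.65 at r = 0.3 and 0.85 at r = 0.7, a gain of 15-35%.

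The pilot SDs (section 3, Table 1, initial to 4-week) were pooled over the two arms as the root mean square. For PCL, baseline is √((10.83² + 11.41²)/2) = 11.12 and follow-up is √((15.59² + 16.68²)/2) = 16.14, so k = 1.45. At r = 0.3 the ratio is 2.106 × 0.91/(1 + 2.106 − 0.871) = 0.86.

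| Outcome | Baseline SD | 4-week SD | k | Ratio over r = 0.3-0.7 |
|---|---|---|---|---|
| BDI | 9.52 | 9.35 | 0.98 | 0.64-0.83 |
| PCL | 11.12 | 16.14 | 1.45 | 0.86-1.00 |
| Intrusive | 6.58 | 9.21 | 1.40 | 0.84-1.00 |
| Avoidance | 5.13 | 8.60 | 1.68 | 0.91-1.00 |
| Hyperarousal | 4.54 | 8.04 | 1.77 | 0.93-1.00 |
| Cortisol | 5.02 | 3.65 | 0.73 | 0.44-0.53 |
| ACTH | 23.47 | 14.81 | 0.63 | 0.36-0.40 |

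The pilot had 4 participants per arm, so these SDs are very imprecise. Table 1 gives none for PSQI, STAXI or CAPS item 24.

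**The case against.** The strongest reply is that little depends on these analyses. The go/no-go rule compares observed responder rates with a 15% threshold and is expressly not a test. The protocol calls the results hypothesis generating, plans no multiplicity adjustment and urges caution in reading significance. A rise from 5% to about 7% in one secondary model is small beside many openly unadjusted tests. All of that stands, and it limits the weight of the point.

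It can also be said that the stay level, forced-in terms and pooling across imputations belong in an SAP that is not at hand. That stands too, and their absence is not the point. The decision to select from the 12 characteristics is stated in the protocol.

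A reader might go further than the documents allow in five ways:
- **That selection itself causes the inflation.** The full model without selection is just as inflated, so merely deleting the stepwise step would not cure it.
- **That the chi-square test is invalid because it ignores site.** It held its level (4.5-5.6% across simulations), and it is a selection-free test of the same outcome.
- **That frequent loss of site shows harm.** Site was dropped in 84% of trials in one simulation, but there it had no effect on outcome, so dropping it was expected and cost nothing.
- **That baseline is ignored altogether.** The responder definition and every change score use it; baseline CAPS and site are both candidates in the logistic model; and for the mixed model the protocol says "military cohort, and site will be explored in the adjusted analysis".
- **That ANCOVA would save 15-35% for every continuous outcome.** That range needs equal SDs at baseline and follow-up, which the pilot data do not show for the PTSD measures.

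**Conclusion.** The point holds as an improvement to secondary and descriptive analyses. The adjusted responder test, at one month and again at three, can be expected to run at roughly 6-8% against a nominal 5%. A short fixed model runs at about 5-6%. The difference is modest, about two percentage points, and rests on an assumed stay level of 0.05-0.10, treatment forced in, and assumed covariate strengths. The less quantifiable cost is that the covariate set may change between imputed data sets and sensitivity analyses.

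For the change scores, the t-tests are valid. The precision available from baseline adjustment depends on the outcome: about 15-35% where SDs are equal (BDI in the pilot comes close), about 0-16% for PCL and the CAPS subscales, and more for four-week cortisol and ACTH. These figures assume r of 0.3-0.7 and, where pilot SDs are used, rest on very few participants.

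The primary decision rule is unaffected.

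**What to change.** - **Adjusted responder analysis (one and three months).** Pre-specify one logistic model with treatment, baseline CAPS and site, with no selection, and use it in every imputed data set and sensitivity analysis. Pool Albuquerque (2 enrolled) with Salisbury and Little Rock (5 to 6 expected each, section 4.0): 2 + 5 + 5 = 12 to 2 + 6 + 6 = 14 participants. Stepwise predictors may be reported separately as exploratory.
- **Chi-square test.** It may stay. A Cochran-Mantel-Haenszel test stratified by the same pooled sites would match the randomisation, but it corrects no error.
- **Change-from-baseline comparisons (Descriptive Outcomes 1b to 7b).** Use ANCOVA with the baseline value and pooled site, and keep the Wilcoxon test as a sensitivity analysis.

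The cost is a change of wording in the analysis section. No data, visits or participants are added.
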